### Randomisation

The sequence was generated using a varying-sized permuted block design, stratified within centre. The sequence was concealed by the central research team on a secure system. The allocation sequences are concealed from analyst and central research team until planned unblinding following interpretation of the study findings. Participants and research staff at the research sites will not be blinded; however, allocation will be random as to not introduce bias.

Potentially eligible participants are randomised and allocated centrally by the research team via e-mail (sent within a secure e-mail network) for the random allocation of potentially eligible participants identified solely via a completely pseudonymous identifier (10-digit NHS Number). Research sites will then receive the 10-digit pseudonymous identifier, a 6-digit Participant Research Number (the first two digits being a site identifier and the subsequent four digits referring to the participant) and the method assigned to. The use of a pseudonymous participant research number is to aid compliance with data governance and to ensure blinding of the participants to the central research team.

### Trial procedure

Potentially eligible participants who have been found eligible by a member of their own clinical care team acting as principal investigator (PI) at the research site, will firstly be randomly allocated to each of the four arms of the study. Following random allocation, potentially eligible participants will be asked to consent by the PI to the research study based on the method of administration they have been randomly allocated. The potentially eligible participants will receive an Invitation Letter, a Participant Information Sheet and a Consent Form via the post. The participant facing documentation will invite the participant to consent to the study and receive their 6-month review and the PRHSQs via one of the four methods they have previously been randomly allocated. Additionally, a proxy consent option is noted in the Participant Information Sheet and Consent Form, thereby allowing for a designee to offer consent on behalf of the participant via the principles of informed consent if the participant requires physical assistance to complete the questionnaire.

Following the initial contact, participants who have not responded will be contacted a second time; two working weeks following the dispatch of the first letter. The second contact will contain the same information as the initial contact (Invitation Letter, Participant Information Sheet and Consent Form). Potentially eligible participants will be given a further four working weeks to reply to the second invitation to participate. If no consent is returned, the potentially eligible participant will be assumed not to wish to take part and will not be asked to complete the PRHSQs.

For all potentially eligible participants who are randomised and invited to participate in the study, we will collect a range of background demographic data and a small number of routinely collected health-related data. See Table 1 for details of data for collection.

**Table 1 Tab1:** Demographic and routine clinical data for collection

Demographic data	Routinely collected clinical data
Date of birth DD/MM/YYYY	Classification of stroke: Cerebral Infarct (ICD I63) Cerebrovascular Haemorrhage (ICD I61) Stroke – not specified as Haemorrhage or Infarction (ICD I64)
Sex	Date of index event (date of stroke) Individual National Institutes of Health Stroke Score (NIHSS) on admission: 0–42
District-level postcode – First 3–4 digits of a UK post code	
	Treated with thrombolysis? Yes / No
	Modified Rankin Score on discharge or transfer from stroke unit: 0–6
	Clinically confirmed diagnosis of aphasia as sequela of ICD I63, I61 or I64?: (data collected at 3 sites within a single Health Board only) Yes / No

All demographic data and routinely collected clinical data will be stored against a Participant Research Number in the research data base. Personally identifiable information will only be stored at the research sites and will not be stored for those who do not offer informed their consent before the cut-off period of 4 weeks following the posting of the second letter Therefore, no personally identifiable information will be held by the central research team.

All consented participants will receive the PRHSQs. The PI at site as a member of both the research team and the participant’s own care team will be responsible for arranging or delegating the completion of the questionnaires between 4 and 8 months post stroke. There are schema for each method by which the PI must abide; however, the methodologies for all four methods of administration differ slightly and are as follows:

#### Face-to-face interview

As part of their routine care, the consented participants will receive a 6-month post-diagnosis review appointment with either a clinical nurse specialist (CNS) in stroke or their clinician. During the 6-month post-stroke review appointment the PRHSQ will be administered by a member of the research team. If participants fail to attend the designated appointment they will not be contacted as part of the study but may potentially be followed up by their own care team at a later date.

#### Telephone interview

The consented participants will receive through the post an appointment time to receive a telephone interview for the 6-month post-diagnosis review appointment with either a CNS in stroke or their clinician. During the 6-month post-stroke review appointment the PRHSQ will be administered by a member of the research team. If participants fail to meet the agreed appointment, they will not be contacted again by the research team, but may potentially be followed up by their own care team at a later date.

#### Postal questionnaire

The consented participants will receive a paper version of the PRHSQ. In addition, participants will receive a pre-paid envelope to return it to the research team. The questionnaire will be answered and filled in by either the participant or designated proxy if the participant is unable to physically complete the questionnaire. If participants fail to respond, they will not be contacted again by the research team, but may potentially be followed up by their own care team at a later date.

#### Online questionnaire

The consented participants will receive a postal invitation to access a secure online version of the PRHSQ via a secure web address (Bristol Online Survey – https://www.onlinesurveys.ac.uk/).. The online questionnaire will be answered and filled in by either the participant or designated proxy if the participant is unable to physically complete the questionnaire. If participants fail to complete the online questionnaire, they will not be contacted again by the research team, but may potentially be followed up by their own care team at a later date.

### Data management

Data will be collected at the research sites until February 2018. Potentially eligible participants who do not respond or consent will not be excluded from data analysis of their demographic and routinely collected non-identifiable clinical data as this data is essential for the determination of acceptability of the methods under investigation. However, individuals who do not consent will not receive the PRHSQs.

Two levels of data management exist for this research study. The first level is that of the individual research site which will have access to identifiable patient data. This will allow the site to invite potentially eligible participants and to contact participants who consent to receive the PRHSQs via the method randomly assigned. Following completion of the PRHSQs the anonymous data received from the two self-administered questionnaires (postal or online) will be populated in the research data base against the corresponding Participant Research Number as detailed on the returned PRHSQs. The data from the two administered methods (face-to-face or telephone) will be captured via anonymised PRHSQs, identified solely by the Participant Research Number.. Data is to be initially coded and entered into a site level data base. The data base has been developed using Microsoft Excel 2013 to support ‘data validation’ and will not accept any data entered outside pre-defined ranges for each discrete data value to be collected. Additionally, ‘conditional formatting’ will be utilised to ensure that double entry is minimised..

The second level of data management is that of the central research team. No personally identifiable information will be transferred or held in the central research data base. Research sites will transfer data to the research team using the Participant Research Number as the unique discriminator. Data quality will be ensured by the trial statistician ([name], Senior Lecturer in Biostatistics, King’s College London) by conducting central data verification prior to data base lock. Data queries arising from data verification procedures will be submitted to sites in writing and sites will have two working weeks to respond in full.

All data will be handled by research sites and by the central research team in accordance with the Data Protection Act (1998) [23]. Subsequent to the closure of the study all trial materials will be archived for a period defined by Good Clinical Practice (ICH-GCP). The study will be conducted in accordance with the Declaration of Helsinki.

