### Outcomes

#### Primary outcome

The proportion of individuals eligible for the study who return the method specific PRHSQs in each of the four study arms (postal, online, face-to-face and telephone)

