### Trial status

Recruitment commenced in July 2017 and is planned to continue until February 2018. Protocol Version: 1.0 Date: 10 April 2017.

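### Recruitment and data collection end in the same month, and entry and completion share the 8-month limit, so some late entrants may lack time to consent and complete yet count as non-returns

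*Protocol article*

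**What the plan says.** **Calendar.** Trial status: "Recruitment commenced in July 2017 and is planned to continue until February 2018". Data management: "Data will be collected at the research sites until February 2018". The article states no collection period after recruitment closes and no earlier last date for randomisation.

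**Time since stroke.** The Inclusion section and Study design admit patients from 4 up to and including 8 months after a confirmed stroke. Trial procedure makes the PI responsible for "arranging or delegating the completion of the questionnaires between 4 and 8 months post stroke". The upper limit is the same for entry and for completion.

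**Steps in between (Trial procedure).** Randomisation comes first: "Following random allocation, potentially eligible participants will be asked to consent by the PI to the research study". Then "participants who have not responded will be contacted a second time; two working weeks following the dispatch of the first letter", and after that "Potentially eligible participants will be given a further four working weeks to reply to the second invitation to participate". Only people who have consented go on to the questionnaire, through an appointment (face-to-face, telephone), a mailed paper form (postal) or a mailed invitation to a web address (online).

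**Primary outcome.** "The proportion of individuals eligible for the study who return the method specific PRHSQs in each of the four study arms". The denominator is everyone eligible, including those who do not consent. The Discussion confirms that all eligible people are accounted for.

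**The concern.** Return of the questionnaire is the primary outcome, and it is read as a measure of acceptability. A person randomised in late February 2018, or close to 8 months after stroke, meets every stated entry rule but may not have time for the trial's own sequence of letter, reminder, consent and questionnaire. That person is then counted exactly like someone who declined the method.

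The margin is 2.5 percentage points, or about 5 returns among 202 per arm (0.025 × 202 = 5.05). Administrative non-returns are therefore not negligible beside it. The section on missing data says that the aim is to learn whether missing responses are systematically more likely in the comparator arms. Non-returns caused by the timetable blur that question.

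**Working it through.** The plan gives no figure for how many entrants would be short of time, so there is none to reproduce. The stated 202 per arm is used below only to turn shares into counts.

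**Inputs from the article**
- Recruitment and data collection: July 2017 to February 2018 (Trial status, Data management).
- Entry window: 4 to 8 months post stroke (Inclusion).
- Maximum consent period: 2 + 4 = 6 working weeks (Trial procedure), taken as 42 calendar days with public holidays ignored.

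**Assumptions, not in the article**
- The calendar runs from 1 July 2017 to 28 February 2018, which is 242 days or 242/7 = 34.6 weeks.
- Accrual is uniform over that period.
- Time since stroke at entry is uniform over the four-month window, which is 4 × 30.44/7 = 17.4 weeks.

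**Share of entrants with less than t weeks left** = t / length of the period.

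| Time needed | Before end February 2018 | Before 8 months post stroke |
|---|---|---|
| 6 weeks (maximum for consent) | 6/34.6 = 17% (35 of 202) | 6/17.4 = 34% (70 of 202) |
| 2 weeks | 2/34.6 = 6% (12 of 202) | 2/17.4 = 11% (23 of 202) |

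The full reply period cannot be honoured for anyone randomised after about 17 January 2018 (28 February less 42 days), or later than 8 − 42/30.44 = 6.6 months after stroke. The two columns overlap and must not be added. The time to deliver and complete the questionnaire after consent is not stated, so none is added.

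**Effect of equal proportional loss.** If a share f of returns is lost in both arms, rates p1 and p2 become p1(1 − f) and p2(1 − f), and the difference d becomes d(1 − f).
- d = 5.0, f = 0.17: 5.0 × 0.83 = 4.15, about 4.2 points.
- d = 5.0, f = 0.06: 5.0 × 0.94 = 4.7 points.
- At f = 0.17, true differences up to 2.5/0.83 = 3.0 points would fall inside the 2.5-point margin.

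The value f = 0.17 supposes that every entrant exposed to the calendar limit is lost, so it is an upper illustration.

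**The case against.** **Six weeks is a ceiling.** A reader might infer that late entrants are forced non-returns. The documents do not support that. Someone who answers the first letter promptly can go straight on to the questionnaire. Only those entering in the last days of February 2018, or almost at 8 months, have practically no chance. The rest are at risk, so the six-week shares are upper figures for the consent step. This objection stands.

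**The 8-month limit is a duty on sites.** The primary outcome carries no time limit, and nothing says that a questionnaire returned after 8 months is discarded. This also stands. The 8-month part of the point depends on sites keeping to the completion window as written. The calendar part does not.

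**Entry need not be uniform.** The trial is built around a 6-month review, so entry may cluster nearer 6 months, which would lower the 34%. That is fair, and the figure is labelled as resting on the assumption.

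**Unequal loss by mode.** A reader might also infer that face-to-face loses more returns because it needs an appointment, which would bias online and postal towards non-inferiority. The article gives no times by mode. Postal and online also need a mailing after consent, and face-to-face uses a routine review that most patients already expect. Randomisation in blocks within centre should balance the number of late entrants across arms. Neither unequal loss nor its direction can be claimed, nor that it would use up the margin.

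**Condensed article.** The full protocol may set an earlier last randomisation date. That is possible, but the point rests on dates and windows that the article does state and that do not fit together.

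**Precision.** Lower return rates also widen the interval: from 85% to 0.85 × 0.83 = 70.6%, the variance p(1 − p) rises from 0.128 to 0.208. This works against a non-inferiority claim. The shrinkage argument concerns the estimated difference, not the net error rate.

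**Conclusion.** The conflict between the stated rules is real. Recruitment and site data collection share an end month, and entry and completion share an upper limit, with up to six working weeks of consent in between and every eligible person in the denominator. Followed as written, some late entrants may become non-returns for reasons unrelated to acceptability.

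Under uniform accrual and uniform time since stroke, the consent period alone exposes at most about 17% of entrants to the calendar limit and about 34% to the 8-month limit. If two weeks suffice, the shares are about 6% and 11%. These are shares at risk, not shares lost.

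The effect by mode is unknown. Unequal loss is not needed for the point to matter, because equal proportional loss already pulls a true difference towards zero, the direction that favours non-inferiority. The passages should be reconciled; the fault does not by itself invalidate the comparison.

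**What to change.** Reconcile Inclusion, Trial procedure, Data management and Trial status in two respects.

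1. **Calendar.** Either state a last randomisation date that leaves time for the consent period plus completion before data cut-off, or keep data collection open for that period after the last randomisation. The period should be the same in all four arms.
2. **Time since stroke.** Reconcile the upper entry limit with the consent period and the 8-month completion limit, so that anyone admitted can go through the stated process. Which limit should move is for the investigators to decide, and the timing of the clinical review itself is not at issue.

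The cost is a slightly longer data-entry period or an earlier stop to recruitment, and possibly a slightly narrower entry window.

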### Monitoring

Site monitoring visits will occur throughout the conduct of the study. These monitoring visits will be conducted by members of the central research team and will ensure the correct conduct of the study and will identify any protocol deviations. Furthermore, site monitoring visits will support sites and will offer the opportunity for the central research team to improve the conduct of the study by identifying needs at the research site and offer any clarification or training necessary. The principal investigators (PIs) at research sites are responsible for monitoring protocol deviations and sites are required to report all deviations via the protocol deviation form. All deviations will be monitored and assessed by the central research team. Following assessment, corrective and preventative actions will be disseminated to the sites.

### Adverse events

All harms will be reported utilising an adverse and serious adverse event (AE, SAE) form included in the research site file, which will be disseminated to all research sites during site initiation visits. We do not anticipate any trial-related AEs; however, sites will collect and report all AEs and SAEs to the central research team within 24 h of discovery as per the Health and Care Research Wales guidelines. In the event of a trial-related AE or SAE the research site will escalate this to their local NHS R&D department, National Research Governance Organisation and to the chief investigator (CI). Additionally, all PRHSQs can be unblinded via the research sites in the rare event that a concern for patient safety or the safety of others is identified.

### Outcomes

#### Primary outcome

The proportion of individuals eligible for the study who return the method specific PRHSQs in each of the four study arms (postal, online, face-to-face and telephone)

#### Secondary outcomes

The proportion of individuals eligible for the study who return the method specific PRHSQs in each of the four study arms (postal, online, face-to-face and telephone) for individuals with communication issues (i.e. aphasia)The proportion of individuals eligible for the study who return the method specific PRHSQs in each of the four study arms (postal, online, face-to-face and telephone) by stroke severity as defined by individual NIHSS on admissionThe proportion of individuals eligible for the study who return the method-specific PRHSQs in each of the four study arms (postal, online, face-to-face and telephone) by stroke type; Cerebral Infarct (ICD I63), Cerebrovascular Haemorrhage (ICD 161) or Stroke, not specified as haemorrhage or infarction (ICD I64)

### Statistical analysis

#### Analysis of the primary outcome

We will carry out a difference of two proportions between the three intervention groups (postal, telephone or online) verses face-to-face administration, with a 2.5% non-inferiority margin. The three comparisons will be adjusted using a Holm [24] multiplicity adjustment, with a two-sided alpha = 0.05. The analysis will be presented as a difference with an associated 95% confidence interval (CI).

Analyst and researchers blinding to the allocation will remain in place until interpretation of the primary and secondary outcomes are agreed. Following un-blinding of the allocation, difference will be generated in the three comparator allocation groups, and face-to-face completion rate, and will include the non-inferiority margin of 2.5%, as our primary analysis.

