## Methods/design

### Study design

This study is a UK four- arm, pragmatic, multicentre, non-inferiority randomised controlled trial of the method of administering the PRHSQs at the 6-month post-stroke time point (clinically confirmed stroke diagnosis ≥ 4 months to ≤ 8 months). The ratio of allocation is 1:1:1:1, with face-to-face being the method of administration against which the non-inferiority of the three comparator methods (online, postal and telephone) will be discerned. Participants will be randomly allocated to one of four methods of administering these 15 Patient-reported Health Status Questions at eligibility and asked to consent via the post. By virtue of the fact that any of the four methods under investigation are established practices in UK stroke services, participants will not be informed about the other possible modes of administration. Addressing this research question requires implementation of a Zelen design [19] this acknowledges the issues of contacting patients prior to obtaining consent. The impact of this design is due to the nature of the intervention, approaching participants later than usual, as well as a larger-than-usual sample size. We acknowledge that informing participants of the alternative methods of administration may introduce bias, as the rate of return of the PRHSQs for the different assessment methods is the primary outcome of interest. Therefore, participants will knowingly consent to receive and complete the PRHSQs via a single method of administration. See Fig. 1 for the participant flow diagram The study protocol was written in full compliance with the Standard Protocol Items: Recommendations for Interventional Trials (SPIRIT) 2013 [20] and a completed SPIRIT Checklist and Figure 2013 (Fig. 2) [21] are available as a supplement (Additional file 1).

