### Study setting

The study will be undertaken in 14 centres across England and Wales. Centres acting as research sites will be those who were previously involved in potentially eligible participants’ post stroke care. In line with the time-frame of the study, the majority of potentially eligible participants will reside in the community and will be anticipating routine clinical follow-up from the centres acting as research sites.

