#### Secondary analysis of the primary outcome

We plan to repeat the primary analysis after adjustment for: age; sex; National Institutes of Health Stroke Score (NIHSS) on admission and stroke type (Haemorrhagic or Ischaemic).

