### Analysis of the secondary outcomes

Continuous data will be summarised descriptively, and also with a general linear model, and adjusted for patient age and sex. Dichotomous data will be summarised descriptively and will analysed using a logistic regression adjusted for: patient age and sex.

We note that many data will be gathered relating to the questionnaire itself. This useful clinical data warrants publication in its own right; however, it is not the focus of this study and will form a separate stand-alone analysis.

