## Discussion

This pragmatic randomised controlled trial will provide insight into the optimal method of PROM delivery in stroke survivors and also inform the choice of delivery method across other chronic disease conditions, especially conditions associated with chronic physical disability. The choice of a pragmatic study design, whilst offering good generalisability and the testing of a hypothesis under as near to ‘real-world’ conditions as is possible, can and will offer substantial challenges. The ‘natural’ organisational variances of each research site, require careful and thorough discussions to ensure that research is not disruptive to routine clinical work and that the research procedures outlined within the protocol are adhered to.

We assume a possibility that the pragmatic design of the research study will not be accessible to all individuals post stoke. Nevertheless, all eligible individuals are to be accounted for in data analysis. It is believed, that this will offer possible correlations as to why certain demographic and clinical features relate to the number of consented participants for each allocated method.

The benefits of this study, to stroke survivors is in the fact that they will offer clinicians and healthcare commissioners early evidence as to which method they find most acceptable, when compared against the most commonly commissioned approach. Moreover, due to the assumption that data is missing not at random, those who do not respond offer useful data. Therefore, any actions taken on the basis of the final analysis of this study can do so in the knowledge that those actions are based on the preferences of all the eligible stroke survivors approached for the study.

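### Randomisation is stratified by centre but the primary risk difference and its adjusted repeat leave centre out; if return rates differ between centres, the confidence interval is wider than the design warrants

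*Protocol article*

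**What the plan says.** - Randomisation: "The sequence was generated using a varying-sized permuted block design, stratified within centre". Centre is the only stratification factor mentioned.
- Study setting: "The study will be undertaken in 14 centres across England and Wales". Study design: "The ratio of allocation is 1:1:1:1".
- Analysis of the primary outcome, on the method: "We will carry out a difference of two proportions between the three intervention groups (postal, telephone or online) verses face-to-face administration", each set against a 2.5% margin and presented as a difference with a 95% confidence interval. No stratum or covariate is mentioned.
- Secondary analysis of the primary outcome, on the covariates: "We plan to repeat the primary analysis after adjustment for: age; sex; National Institutes of Health Stroke Score (NIHSS) on admission and stroke type". The list ends there, without centre.
- Analysis of the secondary outcomes: "Dichotomous data will be summarised descriptively and will analysed using a logistic regression adjusted for: patient age and sex". Centre is absent here too.

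**The concern.** Blocking within centre makes the arms nearly equal in their mix of centres. Differences in return rate between centres then largely cancel from each comparison of a mode with face-to-face. A standard error built from two pooled proportions still counts that variation as noise. If centres differ, the interval is too wide for the design and non-inferiority is harder to show than it need be.

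Differences between centres are plausible. The Background section explains the use of many sites by the large variability of earlier response rates and by the wish to cover rural and urban populations. The article gives no intraclass correlation, between-centre SD or site-level return rate.

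What is at stake is precision. The estimated difference is not biased by leaving centre out.

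**Working it through.** **Inputs from the article.** 14 centres; 202 per arm, 808 in total; margin 2.5 points; 80% power; 2.5% significance level, taken as one-sided. The only face-to-face figure is about 85%, under Non-inferiority margin; the Sample size section does not say that it was the planning rate.

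**Assumed.** Between-centre SD of the return rate, *t*: 0 to 15 points. A return rate *p* of 50% is shown beside 85%. Centre rates are taken as common to the two arms compared.

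**The plan's own figure, for scale.** With equal true rates, n per arm = (1.960 + 0.842)² × 2p(1−p) / 0.025². At 85% this is 7.849 × 0.255 / 0.000625, or about 3,203, not 202. So 202 is not reproduced from the 85% rate. That is a separate matter, but it shows how little the present point can change.

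**Step 1: variance share.** A single return has total variance p(1−p), of which t² lies between centres. Stratified allocation removes that part from the difference, so the share wrongly kept by the unstratified formula is t² / [p(1−p)]. At 85% and 10 points: 0.01 / 0.1275 = 7.8%. This is also the fraction of the sample in effect discarded; 0.078 × 808 is about 63 people.

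**Step 2: standard errors and power.** Unstratified SE = √[2p(1−p)/202]; stratified SE = √[2(p(1−p) − t²)/202]. Power with equal true rates = Φ(0.025/SE − 1.96), before any multiplicity adjustment.

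| Return | SD (points) | Share | Unstratified SE | Stratified SE | SE ratio (unstratified/stratified) | Power, unstratified → stratified |
|---|---|---|---|---|---|---|
| 85% | 0 | 0% | 0.0355 | 0.0355 | 1.00 | 10.4% → 10.4% |
| 85% | 5 | 2.0% | 0.0355 | 0.0352 | 1.01 | 10.4% → 10.6% |
| 85% | 10 | 7.8% | 0.0355 | 0.0341 | 1.04 | 10.4% → 11.0% |
| 85% | 15 | 17.6% | 0.0355 | 0.0322 | 1.10 | 10.4% → 11.8% |
| 50% | 0 | 0% | 0.0498 | 0.0498 | 1.00 | 7.2% → 7.2% |
| 50% | 5 | 1.0% | 0.0498 | 0.0495 | 1.01 | 7.2% → 7.3% |
| 50% | 10 | 4.0% | 0.0498 | 0.0487 | 1.02 | 7.2% → 7.4% |
| 50% | 15 | 9.0% | 0.0498 | 0.0475 | 1.05 | 7.2% → 7.6% |

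**Step 3: simulation.** 14 centres, 808 people, blocks of 4 or 8, 2,500 runs per setting. At 85% return:
- SD 0: true SD of the crude difference 0.0351, mean unstratified SE 0.0354. They agree, as they should.
- SD 10 points: 0.0332 against 0.0352, so the SE is about 6% too large; coverage of the crude 95% interval 96.1%.
- SD 15 points: 0.0320 against 0.0349, about 9% too large; coverage 96.7%.

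**Step 4: is the stratified interval sound with small strata?** Equal sites would hold 808/14 = 57.7 people, or 14.4 per arm. In the simulation the Mantel-Haenszel SE stayed within about 3% of the true SD but fell below it (0.0342 against 0.0352 at SD 0). Its coverage at 85% return was 94.9%, 94.7% and 93.9% at SD 0, 10 and 15 points. The shortfall is the usual one from dividing by n rather than n − 1 in each cell: √(13.4/14.4) = 0.965, and 0.965 × 0.0355 = 0.0342.

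**The case against.** **The effect is small and errs on the safe side.** This stands. Ignoring centre costs precision and does not inflate false non-inferiority. A reader might infer that stratifying would relieve the trial's shortage of power at 2.5 points. It would not: the gain at 85% return and an SD of 10 points is from 10.4% to 11.0%.

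**The size is unknown.** This stands too. A reader might take it as established that the standard errors are too large. That holds only if return rates differ between centres, and the article gives no figure, so the range has to start at zero.

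**The Discussion might seem to settle it.** It speaks of "organisational variances of each research site", which could be read as saying that sites will run the modes differently. The sentence is about keeping the research from disturbing routine work and about keeping to the procedures. Trial procedure also binds each site's principal investigator to a set scheme for each mode. The rural and urban mix in the Background is better support, though it too is unquantified.

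**The logistic models.** A reader might extend the argument to the logistic regressions for secondary outcomes. It does not carry over: adding centre can increase the standard error of a conditional log-odds ratio. Aphasia, moreover, is recorded at only three sites in one Health Board.

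**It belongs in the analysis plan.** Partly fair. The primary analysis text names no estimator or interval method, and a Mantel-Haenszel risk difference is still a difference of proportions. But the article names the adjustment set for the primary outcome and leaves centre out. A plan that followed it as written would do the same.

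**Sites may be unequal.** Recruitment is open-door, without quotas, so 14 per arm per centre is only an average. Mantel-Haenszel weighting tolerates small strata; many fixed centre terms in a regression may not.

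**Conclusion.** The point holds as an efficiency matter confined to the risk difference. The only stratification factor mentioned appears neither in the primary analysis nor in the named adjustment set for the primary outcome. If centres differ, the unstratified interval is conservative. The loss is about 0% to 18% of the sample at 85% return, and 0% to 9% at 50%, for an assumed between-centre SD of 0 to 15 points. The fact of the omission is certain; its size rests wholly on that assumed SD. It is not a threat to validity, and it is minor beside the sample size.

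**What to change.** 1. For each mode against face-to-face, make the primary estimate the centre-stratified (Mantel-Haenszel) risk difference, with its stratified confidence interval set against −2.5 points. Name a variance estimator suited to small strata, such as Sato's or one with n − 1 divisors.
2. Add centre to the adjusted analysis of the primary outcome, and report that analysis as a risk difference. If a model is used, report the standardised difference. A random centre effect is an option if some sites are small.
3. Keep the crude difference as a descriptive figure.
4. Record the choice before unblinding, since changing the estimator of a non-inferiority test afterwards would be post hoc.

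The cost is a sentence or two in the statistical analysis plan. No new data are needed: the Randomisation section says that the first two digits of the Participant Research Number identify the site.
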